## Abstract

**Background:**

The World Health Organization (WHO) is coordinating two randomised controlled trials (RCTs) across three sites in Africa (Ethiopia, Nigeria, and Tanzania) and four in Asia (one in Bangladesh, two in India, and one in Pakistan) to generate evidence on the optimal place of treatment for young infants (YIs) with a single low-mortality risk sign of possible serious bacterial infection (PSBI) and switching antibiotic therapy from injectable to oral in YIs with moderate-mortality risk signs of PSBI. We present the framework and methodology used to compare the costs and evaluate the cost-effectiveness (CE) of these strategies.

**Methods:**

Cost analysis will be conducted from societal (hospital and household) perspectives. Hospital medical costs (staff, medicines, and consumables) and operational costs (inpatient bed costs, non-consumables, training, and communication) will be collected through hospital surveys. Household costs, including medical payments for treatment (registration, consultations, medications, consumables) and non-medical costs (transport, food, and wage loss), will be collected through household surveys. In both RCTs, combined hospital and household (including medical and non-medical) costs for all randomised sick YIs (SYIs) will be used, with an intention-to-treat approach, to calculate the cost per SYI in each study arm. Effectiveness measures, based on the absence of adverse outcomes, will be used to determine incremental CE ratios and incremental net benefits. Separate societal and payer/provider perspectives will be considered, and site-specific willingness-to-pay thresholds will be estimated. The household’s medical and non-medical costs, along with their share of societal costs, will estimate the household burden per treated child.

**Conclusions:**

This CE framework will evaluate thresholds for new PSBI treatment strategies in YIs, integrating health system and household perspectives. It will seek to identify safe, cost-effective approaches to reduce economic burdens, inform national budgetary impact, and potentially prompt WHO guideline revisions to improve infant care in low-resource settings globally.

In 2024, around 2.3 million neonatal deaths occurred worldwide, accounting for 47% of all under-five deaths [1], with infections responsible for up to 37% of these deaths in South Asia and sub-Saharan Africa [2]. The World Health Organization (WHO) recommends hospital referral for inpatient injectable therapy for at least seven days with supportive care, if needed, for young infants (YIs) (0–59 days old) with any sign of possible serious bacterial infection (PSBI) [3,4]. However, in resource-limited settings, a large proportion of the families of YI with PSBI refuse hospital referral due to several barriers, such as distance to the health facility, cost of hospitalisation, daily wage loss during the hospitalisation period and cultural constraints resulting in newborn deaths [5–8].

To address these barriers, several clinical trials [5–12] and research have been conducted in Africa and Asia to assess the feasibility of implementation [13] of the WHO PSBI management guidelines [14] and to establish that YI with clinically severe infection (CSI) and pneumonia (subclassification of PSBI) treated with simplified outpatient antibiotic regimens are effective. Pooled analyses of three trials from Africa and Asia reported that a simplified treatment regimen using oral amoxicillin with gentamicin had better outcomes compared to other regimens in ambulatory settings [15]. Secondary analysis of the African Neonatal Sepsis Trial further highlighted that infants with signs of CSI had higher mortality rates when treated in a hospital compared to outpatient treatment. This secondary analysis further divided these signs into low- or moderate signs based on the case fatality ratio associated with each CSI sign [16].

Cost-effectiveness analyses (CEAs) have become vital in identifying affordable and effective interventions for the management of neonatal sepsis and the reduction in neonatal mortality among vulnerable newborns. A study from Ethiopia assessed the costs of managing PSBI for YI at health posts when a referral was not feasible and found it cost-effective [17]. Similarly, the African Neonatal Sepsis Trial found that management of PSBI with simplified antibiotic regimens was cost-effective in the Democratic Republic of Congo, Kenya, and Nigeria [18]. A systematic review across 14 low-income countries estimated an average hospitalisation cost for YI with sepsis (considering both provider and payer perspectives) at USD 55 [19]. Another multi-centric implementation research in India estimated USD 18.5 as the health system cost for recommended and acceptable outpatient treatment of PSBI with simplified antibiotic regimens [20].

We present a comprehensive cost-effectiveness (CE) methodology for two randomised controlled trials (RCTs) evaluating new treatment strategies for managing PSBI in YIs. The first trial [21] will evaluate the appropriate place of treatment for YI with a single low-mortality-risk PSBI sign, and the second [22] will evaluate the duration of hospitalisation for those with moderate-mortality-risk PSBI signs by switching from injectable to oral antibiotic therapy. Additionally, this framework will provide a methodology to calculate provider and household costs across each study arm, offering a holistic perspective on the economic and clinical impacts of these interventions. The primary objective will be to determine whether the intervention is at least non-inferior to the control in preventing poor clinical outcomes in both RCTs. Additionally, it will use an incremental net benefit (INB) approach to estimate country-level willingness to pay thresholds.

## METHODS

### Study design and participants

We followed the CHEERS 2022 guidelines for economic evaluations (Checklist S1 in the **Online Supplementary Document**) and a trial-based CE framework [23]. The study involves two individual, parallel-arm, open-label RCTs being conducted at 31 hospitals at seven sites in six countries – three sites in Africa (Ethiopia, Nigeria, and Tanzania) and four sites in Asia (Bangladesh, two sites in India, and Pakistan) [21,22]. The study participants will be YI with low- or moderate-mortality-risk PSBI signs that seek treatment from selected hospitals in the study area and live within a catchment area where a follow-up up to day 15 can be accomplished.

### Interventions and controls in the two RCTs

The RCT1 is evaluating whether experimental outpatient treatment (intervention) for YI with a single low-mortality-risk PSBI sign (*i.e.* body temperature ≥38°C, severe chest indrawing, or fast breathing of ≥60 breaths/min in 1–6-day-old infants) with injectable gentamicin (once daily) for two days and oral amoxicillin (twice daily) for seven days can be as effective as the recommended care with injectable ampicillin (2–4 times daily) and injectable gentamicin (once daily) with supportive care for seven days (control) [21]. The RCT2 is evaluating hospitalised YI with moderate-mortality-risk PSBI signs (*i.e.* body temperature <35.5°C, movement only when stimulated, or stopped feeding well), alone or in combination, or multiple low-mortality risk PSBI signs. These infants are treated similarly for the first two days with injectable ampicillin (2–4 times daily, depending on the weight of the YI) and injection of gentamicin (once daily). At 48 hours after starting treatment, if they show clinical improvement in terms of the absence of all signs of critical illness or CSI, and have a negative C-reactive protein (CRP) laboratory test, they are randomised into two groups: one is discharged on oral amoxicillin (twice daily) for five days at home (intervention), and the second group continues injectable antibiotic therapy in the hospital for five more days (control) [22].

### Outcomes

Poor clinical outcomes for RCT1 [21] are death at any time from randomisation up to day 15 of initiation of treatment, any sign of critical illness (*i.e.* no movement at all, unable to feed at all, or convulsions) or any sign suggestive of another serious infection (*e.g.* meningitis, bone or joint infection on day two, four, or eight post-randomisation, any new CSI sign on day four or eight post-randomisation, or persistence of the presenting CSI sign on day eight post-randomisation).

Poor clinical outcomes for RCT2 [22] are death between randomisation (day three of initiation of therapy) and day 14 of initiation of therapy, presence of any sign of critical illness (*i.e.* no movement at all, unable to feed at all, or convulsions) or any sign suggestive of another serious infection (*e.g.* meningitis, bone or joint infection on day four and eight of initiation of therapy, or presence of any sign of CSI on day eight of initiation of therapy).

The effectiveness rates will be estimated for each treatment arm for both RCTs as the proportion or percentage of the population that did not experience poor clinical outcomes. The following formula is used:

Mean effectiveness rate (E) = (positive outcomes (O) / total population (N)) × 100

Where O is the number of individuals with positive outcomes calculated as O = N − P, N is the total number of individuals in each arm of the treatment group, and P is the number of individuals who experienced poor clinical outcomes (*e.g.* death, deterioration, or other conditions described above) among N. Mean effectiveness will vary between enrolled SYI and those who received recommended treatment, as P and N would differ. The effectiveness measure (‘proportion without poor clinical outcomes’) is chosen for its direct alignment with trial endpoints and feasibility across heterogeneous sites.

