Coverage of sick YIs (SYI) assessed, enrolled and treated under both RCT1 and RCT2 for control and intervention.Data on two outcome variables for all SYI covered under different treatment arms. Well-trained independent outcome assessor visits all enrolled cases on days two (only for RCT1), four, eight, and 15 after the initiation of treatment to assess the study outcomes in both intervention and control arms.Average annual salaries of nurses, paediatricians, medical officers and any other staff supporting treatment. To calculate staff costs per minute, data will be collected on the average number of days in a month and the average number of hours in a day that staff work.Staff time will be considered only for activities that are linked to hospital staff and not those linked to research staff, such as outcome assessment or treatment documentation (**Table 1**, **Table 2**). The activities for the staff time will be based on a pre-defined implementation strategy [21,22].Data will be collected for SYI that receive at least 80% of the treatment (recommended treatment) and those who receive <80% of seven-day (<5.5 days) treatment (partial treatment). The latter occurs due to a treatment failure, a change in treatment, readmission, left voluntarily, or death. For the recommended treatment, we will collect costs for the seven-day treatment period following the initial assessment, across both study arms and both trials. For partial treatment, medical costs will be calculated for an average treatment period of three days in RCT1 after the initial assessment, and for two days in RCT2 in both inpatient and outpatient arms after randomisation. Costs for enrolled SYI will be weighted by the proportion of participants receiving 80% recommended treatment and those receiving partial treatment, with weights set to SYI for each group. This prevents any child randomised and enrolled from being missed. Costs due to complications, changes in treatment, and/or readmission are outside the seven-day recommended treatment window in both study arms of both trials and will not be collected.Data on staff time per visit for an activity and the number of visits undertaken for each activity during the recommended treatment period will be collected by interviewing at least 3–5 staff of each type at each hospital.The staff time for all visits during the treatment period will be weighted by the number of days an infant receives the activity and the number of YI receiving the activity (defined as weighted by infant days). For the first activity assessment on presentation at the hospital, the number of SYI will be all enrolled for a given treatment, whether partial or recommended. For all other activities, SYI who receive 80% recommended treatment will be considered to have received seven days of treatment, and those receiving partial treatment for an average of three days to calculate the costs for those enrolled.The average exchange rate used to convert all the cost estimates in local currency into USD will be for 2024, the period for which the salaries of providers, prices and household costs will be reported. It will ensure consistency, and inflation rate adjustments will not be needed for cost calculations. The recommended treatment period will be seven days for inpatient treatment in the control arm and seven days for outpatient treatment in the intervention arm for RCT1. For RCT2, the average length of inpatient treatment is 48–72 hours, prior to a negative CRP laboratory test. In RCT2, the control group after randomisation will continue receiving inpatient care for five days, while the intervention group will be discharged from the hospital on oral amoxicillin for five days to be taken at home. Both arms will share the initial hospitalisation costs during the first two days in RCT2, including CRP test costs (including staff time, kits, and laboratory costs).The data on quantities used of injection gentamicin, injection ampicillin and oral amoxicillin will be as per the recommended treatment and partial treatment per SYI for each treatment arm under each RCT.The number of SYI receiving specific medicines and consumables for each arm under both RCTs will be calculated based on the numbers receiving recommended treatment and those receiving partial treatment.Information on types and quantities of consumables required with each medicine will be collected separately for each hospital and each arm under both RCTs. The cost of medicines and consumables will be charged per size in which they are dispensed. Medicine dosage varies with the weight of the YI [21,22]. Price will be taken for full strength, and the rest will be marked as wastage. Price data will be taken from the hospital's pharmaceutical department (if available); otherwise, the market price or the WHO price will be used.Data on annual financial expenditures and admissions in the newborn intensive care units or paediatric wards where YI with PSBI are treated as inpatients at the hospital will be collected and allocated based on patient days to calculate the inpatient bed costs/ SYI treated as an inpatient. These expenditures include administration, utilities, laundry, security, data management, internet, non-consumables and other costs in the hospital inpatient ward.Hospital ambulance to transport enrolled SYI under a specific treatment arm is a cost to the hospital. It is difficult to get this information separately for each enrolled SYI under different treatment arms from the hospital data. Indirect estimation based on the average trip cost and the number of SYI using free public ambulances, estimated from household data for each treatment arm in RCT1 and RCT2, will be used.Hospital data will also be collected for operational costs, which help to strengthen the assessment, identification, and treatment of SYI with PSBI. These include training, supplies, and communication. The total costs under these three will be estimated per SYI assessed. Staff training costs include the costs of development of training material and training cost per staff per day based on the per diems, honorarium for trainers, venue and refreshment costs. Total training costs will be calculated for all staff who were used to assess and treat SYI and will be estimated per SYI assessed. Training costs for research staff for outcome assessment or data collection will not be collected or included. Price and quantities of supplies used during the assessment, such as timers, thermometers and weighing scales, will be prorated for PSBI assessed. Communication costs, include job aids or educational material, and the cost of videos developed and played at the hospitals for educating the mothers about the danger signs. Data will be collected on item quantities and prices from hospitals to assess total costs and costs per SYI assessed.

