### Strengths and limitations

We integrate economic and clinical evidence to identify safe, cost-efficient treatment strategies that could reduce economic burdens, inform national budgeting decisions, and potentially support revisions to WHO guidelines for improved infant care in low-resource settings worldwide.

A key strength is that the analysis is embedded within a multi-country RCT and incorporates both provider and household perspectives to assess CE from societal and provider/payer perspectives. The use of site-level stratification and INB methods further enhances transparency in quantifying uncertainty and supports decision-making using threshold-based interpretation.

Hospital cost data will be collected from all hospitals that randomise infants into treatment arms and aggregated across sites. Provider and household cost data will be collected over a consistent, recent financial period, ensuring alignment of price inputs and minimising variability due to inflation or exchange rate fluctuations during the multi-year enrolment period. Household expenditures will be collected close to the time of care (day eight, 15, or within two weeks after the 15-day outcome visit), with cross-verification against receipts or facility records where available, thereby reducing recall bias. Provider cost and outcome analyses will include the full randomised cohort, strengthening the robustness of the primary CE estimates.

One limitation is that household costs and wage data will be collected during the final nine months of the study using a purposive sample of approximately 10–15% of enrolled infants in each treatment arm at each site. Although this improves operational feasibility, it may introduce selection bias when estimating non-medical costs if respondents differ systematically from those not interviewed. No imputation or adjustment methods will be applied; although missing data are assumed to be random, non-random patterns cannot be entirely ruled out.

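### Effectiveness is obtained by subtraction (O = N − P) over everyone in the arm, so an infant whose outcome is unknown is scored as a positive outcome

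*Protocol article*

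**What the plan says.** The Outcomes section of the protocol article sets "Mean effectiveness rate (E) = (positive outcomes (O) / total population (N)) × 100". Below the formula it explains the terms, and successes come by subtraction: "the number of individuals with positive outcomes calculated as O = N − P, N is the total number of individuals in each arm". The remaining term, P, counts infants recorded with one of the listed poor outcomes. Those listed for both trials are death within the stated window, signs of critical illness, signs of another serious infection, and signs of clinically severe infection on specified days. Loss to follow-up and a missed assessment are not on either list. The section adds that N and P will differ for the subgroup who received recommended treatment, so the same subtraction applies there.

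Three other places fix the population. Statistical analysis procedures uses the outcomes of all enrolled infants for the ICER. The CEA section takes costs for all randomised infants and assesses effectiveness in the same population. Strengths and limitations states: "Provider cost and outcome analyses will include the full randomised cohort".

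On ascertainment, the Hospital data section has an independent assessor visit every enrolled infant in both arms on days four, eight and 15, and also on day two in RCT1. It gives no rule for a visit that does not take place.

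**The concern.** P can count only poor outcomes that came to light, while N counts everyone in the arm. Whatever is left after subtraction is called positive. That remainder mixes infants who were seen and found well with infants whose status was not established. A death at home that nobody recorded would count as a success.

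Place of care is what these open-label trials randomise, so completeness of follow-up could differ by arm. An arm with more unknown outcomes, other things equal, gains effectiveness. E feeds both the ICER and the INB, and the CEA section itself brings in the INB for cases where effectiveness differences are small and the ICER is unstable. A small artefact in Δe can then matter for the quadrant of the cost-effectiveness plane, and it moves the INB by λ times the bias. The planned confidence interval for the INB rests on variation between sites and would not reveal a bias that the sites share.

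**Working it through.** The article gives no loss rate and no event rate, so there is no figure of its own to reproduce. The check is algebra from the stated formula, followed by an illustration in which every m and q is an assumption.

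**Step 1. What O contains.** In one arm let A be the infants assessed and found without a poor outcome, P the recorded poor outcomes, and M the infants with unknown outcome. Then N = A + P + M, and

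O = N − P = A + M.

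All M unknown infants sit in O.

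**Step 2. Overstatement of E.** Let m = M/N and let q be the true poor-outcome risk among the unknown infants.

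- Formula: E = 100 × (N − P)/N
- True value: E = 100 × (N − P − qM)/N
- Difference: 100 × m × q percentage points

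**Step 3. Bias in Δe.** With subscript 1 for intervention and 0 for control, the bias is 100 × (m₁q₁ − m₀q₀). It is zero only if the two products are equal.

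**Step 4. Illustration.** q is taken as equal in both arms, and the intervention arm is given more unknowns.

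| m₁ / m₀ | q | Overstatement of E, intervention / control (points) | Bias in Δe (points) |
|---|---|---|---|
| 5% / 1% | 3% | 0.15 / 0.03 | +0.12 |
| 5% / 1% | 6% | 0.30 / 0.06 | +0.24 |
| 5% / 1% | 10% | 0.50 / 0.10 | +0.40 |
| 10% / 2% | 3% | 0.30 / 0.06 | +0.24 |
| 10% / 2% | 6% | 0.60 / 0.12 | +0.48 |
| 10% / 2% | 10% | 1.00 / 0.20 | +0.80 |
| 4% / 1% | 8% | 0.32 / 0.08 | +0.24 |
| 4% / 1% | 20% | 0.80 / 0.20 | +0.60 |

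If the loss rates are swapped between arms, every sign in the last column reverses.

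**Step 5. Equal loss.** With equal m and equal q, Δe is unbiased but each E is still too high: at m = 5% and q = 3%, the formula gives 97.15 where the true value is 97.00. If m is equal but the unknown infants carry the risk of their own arm (p₁ or p₀), the formula gives Δe = (1 − m)(p₀ − p₁). A true difference is then shrunk towards zero by the factor 1 − m.

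**Step 6. What bounds would show.** Take 5% against 1% unknown and a 6% risk among assessed infants in both arms.

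- Formula as written: 94.30 − 94.06 = +0.24 points
- Known outcomes only: 94.00 − 94.00 = 0.00
- All unknowns counted as poor: 89.30 − 93.06 = −3.76
- Unknowns counted as poor in the intervention arm only: 89.30 − 94.06 = −4.76

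The formula reports a single value from a range that it does not disclose.

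**The case against.** The best defence is that the article merely states a binary endpoint and its complement. It takes its outcomes from the two parent trials, whose protocols are not shown and may say how a missed assessment is classified. It nowhere says in words that a missing outcome counts as positive. This has force as regards intent. It does not change the arithmetic, because the article does more than leave the matter open: it prints a formula, a denominator and a population, and together these put unknown infants among the successes.

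The second defence is that loss may be small, and this stands. Assessor visits are planned for every enrolled infant in both arms. Study design and participants limits enrolment to a catchment where follow-up to day 15 can be achieved. Table 2 makes feasible follow-up a condition of randomisation in RCT2.

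Some stronger readings are tempting, but the documents do not support them.

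- A reader might infer that success is never observed under this plan. The planned visits mean that most successes may well be observed; the defect concerns only infants whose status is unknown.
- A reader might take the Hospital data sentence "The latter occurs due to a treatment failure, a change in treatment, readmission, left voluntarily, or death" as showing that missing outcomes are expected. It lists reasons for receiving less than 80% of treatment. An infant who leaves treatment is still due an assessor visit.
- A reader might see a contradiction with "No imputation or adjustment methods will be applied; although missing data are assumed to be random". That sentence stands in the paragraph on the household cost sample and does not govern clinical outcomes.
- A reader might conclude that the formula favours the intervention or will turn a worse result into dominance. With an assumed bias of 0.6 points, a true Δe of −0.3 would appear as +0.3. With 0.24 points it would appear as −0.06 and keep its sign. If inpatient families were the harder ones to follow, the bias would favour control.

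**Conclusion.** The point holds as a should-fix. Applied as printed, the rule scores every infant of unknown status as a positive outcome, overstates E in each arm by 100 × m × q points, and biases Δe by 100 × (m₁q₁ − m₀q₀) points. Under the assumed inputs the bias in Δe runs from 0.12 to 0.80 points. These sizes rest wholly on assumed m and q, and the documents settle neither the size nor the direction. With near-complete follow-up the effect would be negligible, and a count of unknown outcomes by arm would show that. Since the article allows for small effect differences, the consequence for Δe, the ICER and the INB should be demonstrated and not taken to be nil.

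**What to change.** In the Outcomes section, replace the subtraction by a direct count. Define O as infants observed without a poor outcome: the required sign assessments were done and vital status is known to the end of the death window for that trial.

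Restate the denominator at the same time, in one of two ways:

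- take E over infants with known outcome status (observed poor plus observed not poor); or
- take E over all randomised infants, with unknowns handled by a stated method such as imputation.

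Changing O while leaving N as it is would score every unknown as a failure, so both must change together.

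Report the number with unknown outcome by arm. Add two sensitivity bounds: all unknowns counted as poor, and unknowns counted as poor in the intervention arm only. Carry the same E into the ICER and the INB, and apply the same rule to the subgroup who received recommended treatment.

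The cost is a few sentences and a little more analysis. The article reports data collection as complete, so no new data are needed. E may become slightly less favourable in both arms.
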